### **The objective of the current study**

**Objective:** To experimentally test a new treatment approach for the DTAP treated in the Specialist health care

**How:** This will be achieved by combining the individually tailored cET in a group format (maximum six patients in each group, 1:1 patient: therapist ratio) with DCS/ placebo administered to patients with Obsessive Compulsive Disorder who have failed to respond to or relapsed after receiving ERP treatment

**Hypothesis:** Both DCS (100 and 250 mg) and placebo groups will show a significant improvement, but the patients who receive DCS will maintain the treatment effect significantly better than the placebo group. Thus, differences will occur at the follow-ups.

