### **8.5 Therapist competence and compliance**

All the 4-day treatment groups are led by two experts on the 4-day format together with OCD-therapists who must have participated in the extensive national training program (24) or document equivalent level of training.

In each treatment group the ratio between patients and OCD-therapists will be 1:1 and two experts on the 4-day concentrated format (cET) will participate in each group, which implies direct observation of the therapists.

In order to qualify as a cET-expert, therapists must in addition to being an OCD-therapist, have participated and received supervision in a minimum of two cET groups and demonstrate competency in the exposure procedure in accordance with the OCD CORE competencies (Steketee, Foa and Kozak, 2010) relevant for the 4-day format evaluated independently by two cET experts. Specific competencies required for the 4-day format will be recorded and evaluated separately. Evaluation of competency of the 4-days experts will be repeated every 6 months by the aims of video-taped role-played scenarios as well as multiple choice tests covering typical scenarios which will be rated independently by two cET-experts.

During the study, all therapists participating will be evaluated both for competency and adherence independently by the two cET experts who participate in the group each day. Relevant items in the OCD CORE competencies form will be employed, and the evaluation will be done at the end of each of the two days with exposure. Feedback to the therapists will be provided each day, and if the competence of a given therapist is not acceptable, the therapist will be required to act as an observer the remaining time of the group.

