### **9.6 Treatment**

- **Day 1 Psycho-education and treatment preparation (3 h)**

Participants receive psychoeducation focused on the rationale behind the cET treatment which emphasizes the differences between this approach and the ERP they previously have received. Relevant exposure tasks will be decided upon. The patients are introduced to the micro-intervention “Leaning into the anxiety” (LET), which is to be practiced throughout the two days of exposure

- **Day 2 (8 hrs) and 3(8 h + 2 h psychoeducation for family): Therapist assisted Exposure and response prevention combined with DCS/ placebo**

Patients will engage in individually tailored and therapist assisted ERP, using the micro-intervention LET. Exposures will be conducted in a variety of settings with high ecological relevance, most of them out of the office. DCS on day 2 (first day of exposure) will be taken after 3 hours of the cET. DCS on day 3 will be given approximately 1 hour before the first exposure session of the day.

On day 3 the patient’s family/ significant others are invited to a 2 h psychoeducation.

- **Day 4: Summarizing and relapse prevention**

Summarizing (“lessons learnt”) and planning self-exposures for the next three weeks. Focus will be on teaching the patients how to be “their own therapists. The patients are provided with written information covering procedures and times for upcoming assessments. The patients will, in a group setting, give structured feedback/ evaluation of the treatment at the end, and will prepare exposure tasks to be performed the first three weeks after the treatment.

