### 11.2 Treatment Assignment/ Randomization

Patients are upon inclusion randomly assigned to DCS or placebo using a 2:2:1 ratio of 250 mg DCS: 100 mg DCS: placebo. In order to control for potential interaction effects with antidepressants (121), patients will be stratified on current anti-depressive medication or not. Within each subgroup patients will be randomized in blocks of 5 into ERP+DCS 100 mg, ERP+DCS 250 mg, or ERP + Placebo in the proportions 2:2:1.

A research unit at Karolinska Institute, Sweden, which is not involved in the study, will be responsible for the randomization. Randomization lists will be sent directly to Kragerø pharmacy that will be responsible for providing the medication for patients enrolled.

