## 13. Statistics and Data Management

### 13.1 Statistical Analysis

Statistical analysis will be performed by the investigator and specially designated collaborators and quality controlled and cross-checked by independent party

The primary objective is to demonstrate superiority of concentrated ERP + DCS vs. concentrated ERP + placebo at significance level of  $< 0.05$  (5%). Data will basically be analyzed using intention to treat methodology with a mixed models design, accounting for missing data, with relevant covariates for a given analysis. Data will primarily be analyzed employing multivariate methods (ANOVAs/MANOVAs) with repeated measurement.

Covariates are described in the moderator section (Chapter 6.5). Missing data will be replaced (multiple imputation methods). There will be calculations of effect sizes (Cohen's effect size) for all primary and secondary endpoints. Other relevant multivariate statistical analyses will be performed if relevant to elucidate results of importance to the objectives of the study. Safety data (e.g. side effects) will be collected and summarized in the study results.

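### Exposure treatment is given in groups of up to six with shared lead experts, but the primary analysis named in section 13.1 has no treatment-group term; naming one is a cheap improvement

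*Protocol*

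**What the plan says.** Section 3 (The objective of the current study) describes an individually tailored treatment in a group format, "maximum six patients in each group", with one therapist per patient. Section 8.5 adds that "All the 4-day treatment groups are led by two experts on the 4-day format". These experts rate the therapists after each exposure day and can move one to an observer role for the rest of that group.

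Patients are randomised individually: "Patients are upon inclusion randomly assigned to DCS or placebo using a 2:2:1 ratio" (section 11.2). The only stratification factor is antidepressant use, with blocks of five. The protocol does not say how randomised patients are assembled into treatment groups.

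Section 4 names arm as the between factor and assessment point as the repeated factor. Section 13.1 first mentions an intention-to-treat mixed model with relevant covariates, without random effects, and then states: "Data will primarily be analyzed employing multivariate methods (ANOVAs/MANOVAs) with repeated measurement". It refers to section 6.5 for covariates; that list contains no group, site or therapist variable.

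The hypothesis in section 3 has two parts. Both DCS doses and "placebo groups will show a significant improvement", and DCS will hold its effect better than placebo at follow-up. Section 13.1 makes DCS versus placebo the primary objective.

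**The concern.** Members of one treatment group share lead experts, dates and group sessions, so their outcomes may be correlated. Repeated-measures ANOVA/MANOVA handles the correlation between one patient's visits but takes different patients as independent. With a positive intra-group correlation (ICC), this has two consequences.

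- Within an arm, the standard error of mean improvement is too small, so the interval is too narrow. This touches the first part of the hypothesis and the precision around within-arm effect sizes.
- Between arms, patients on different arms usually sit in the same group, so part of the group effect cancels. Leaving group out of the model keeps between-group noise in the error term and wastes some precision on the primary contrast.

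**Working it through.** **Inputs.** From the protocol: 160 patients, 64/64/32, d = 0.50, alpha 0.05 (section 13.2); 2:2:1 in blocks of five within two strata (section 11.2); at most six per group (section 3). Assumed, because the protocol gives no value: ICC 0.05, 0.10 and 0.20, and every group full at six.

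**The plan's own figure.** Two-sided, 64 versus 64 gives 80.2% power, which matches the stated 80%. The pooled DCS versus placebo comparison, 128 versus 32, gives 71.0%. That gap is a separate matter; 71% is used here only as the base from which a group term gains.

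**Within an arm.** A patient in an arm with share p of the allocation expects (m − 1) × p group-mates on the same arm, so

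design effect = 1 + (m − 1) × p × ICC; true/naive SE = √(design effect); coverage = 2Φ(1.96/√(design effect)) − 1.

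Example, one DCS arm (p = 0.4) at ICC 0.10: 1 + 5 × 0.4 × 0.10 = 1.20; √1.20 = 1.095; 1.96/1.095 = 1.789; coverage 92.6%.

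| Arm | Quantity | ICC 0.05 | ICC 0.10 | ICC 0.20 |
|---|---|---|---|---|
| One DCS arm, p = 0.4 | design effect | 1.10 | 1.20 | 1.40 |
| | coverage, formula | 93.8% | 92.6% | 90.2% |
| | coverage, simulated | 94% | 94% | 91% |
| Placebo, p = 0.2 | design effect | 1.05 | 1.10 | 1.20 |
| | coverage, formula | 94.4% | 93.8% | 92.6% |
| | coverage, simulated | 94% | 94% | 94% |
| DCS pooled, p = 0.8 | design effect | 1.20 | 1.40 | 1.80 |
| | coverage, formula | 92.6% | 90.2% | 85.6% |
| | coverage, simulated | 92% | 90% | 87% |

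The simulated rows use 1,500 trials per setting with the section 11.2 allocation. The Monte Carlo standard error is about √(0.94 × 0.06/1500) = 0.6 points. The formula is mostly a little lower because it takes allocation as unrelated to group, whereas blocking can spread the arms over the groups more evenly.

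**Between arms.** Pooled DCS versus placebo, 3,000 simulated trials per setting, ordinary least squares against a REML random intercept for group:

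| ICC | SE, no group term | SE, group term | Reduction | Power, without → with | Type I error, no group term |
|---|---|---|---|---|---|
| 0.05 | 0.197 | 0.194 | 1.5% | 71.3% → 72.2% | 5.0% |
| 0.10 | 0.197 | 0.190 | 3.6% | 71.6% → 74.2% | 4.3% |
| 0.20 | 0.197 | 0.182 | 7.6% | 72.1% → 77.3% | 3.8% |

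Reductions are 0.003/0.197, 0.007/0.197 and 0.015/0.197. The 1,500-trial runs gave about 71% → 72%, 72% → 73% and 72% → 78%. Together the gain is about 1 to 6 points.

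**Is the unadjusted between-arm SE wrong?** If each group held the arms in exact 2:2:1 balance, true/naive SE would be √(1 − ICC): 0.975, 0.949 and 0.922 at ICC 0.05, 0.10 and 0.15. Section 11.2 does not block by group. Under the allocation as written, the simulated ratio over the same ICC range is 0.96 to 1.00 and the type I error of a one-dose comparison with placebo is 4.2% to 5.1%.

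**The case against.** The strongest reply is that a mixed model's random effects are normally fixed in the SAP, which is not shown. That stands as far as it goes: an unlisted random effect is not an error, and nothing in section 13.1 excludes a group intercept. A reader might infer that the protocol declares patients independent; it does not. What remains is that section 13.1 itself names ANOVA/MANOVA as primary and section 4 lists its factors, and that method has no place for group.

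A reader might also infer that the DCS versus placebo interval is generally too wide. That needs arms balanced inside treatment groups, which section 11.2 does not provide. The unadjusted interval is valid to mildly conservative; the loss is efficiency.

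The ICC may also be small. Each patient has a therapist, "Patients will engage in individually tailored and therapist assisted ERP" (section 9.6), and blinded assessors outside the treatment do the ratings. Six is a maximum, and smaller groups weaken the effect: with four, the true/naive SE for one DCS arm at ICC 0.10 is √(1 + 3 × 0.4 × 0.10) = 1.058 rather than 1.095. These features may lower the correlation but do not make it zero.

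Finally, no decision rule rests on within-arm improvement, which is expected in every arm. Interval width changes; a significance verdict probably does not.

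**Conclusion.** The point holds as a cheap improvement to the method named in section 13.1. For an assumed ICC of 0.05 to 0.20 and groups of six, unadjusted within-arm intervals cover about 91% to 94% for one DCS arm, 94% for placebo, and 87% to 92% for pooled DCS. Pooled DCS is the worst case, since it holds 80% of patients, whereas the hypothesis concerns each arm. The primary contrast is not threatened: type I error stays at or slightly below 5%, and about 1 to 6 points of power are forgone.

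All sizes depend on the assumed ICC and on full groups. The calculations use the arm mean of a single outcome; for improvement from baseline, the relevant ICC is that of the change score, which may differ.

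**What to change.** In section 13.1, make the mixed model the primary Y-BOCS analysis and give it a random intercept for treatment group. Record a treatment-group identifier for each patient; Table 1 lists none. Use the same term, or standard errors robust to grouping, for within-arm change and response rates.

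The cost is about one sentence in section 13.1 and one variable in the data set. The downside is one more variance component, over at least 27 groups if all are full (160/6 = 26.7), with little or no gain if the group correlation is near zero. Sample size, randomisation and treatment are unchanged.

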## 4. Design

The current study is a randomized, double-blind factorial design with DCS (250 or 100 mg) or placebo as between factors and assessment points as repeated factor. All patients receive concentrated ERP treatment. Assessments will be performed at baseline (T0), post-treatment (T1), and at follow-up after 3 (T2) and 12 months (T3) as well as after 5 years (T4).

For overview of study design, see Figure 1.

[figure not shown]

Figure 1 *Overview of the study design*

## 5. Inclusion and exclusion criteria, withdrawal

All 15 OCD-teams in Norway refer patients to the study, thus providing nationwide coverage of relapsed or non-responsive OCD patients.

A maximum of 160 patients will be included (see p.31 for power calculations) within the period from October 2015- June 2018.

Through the National OCD-implementation project all OCD-patients in Norway are ensured access to evidence based treatment. Standardized procedures for collection and storage of data (quality databases) are also established. These data will serve as reference data for standard treatment response, as well as provide detailed information regarding the first treatment-course for the relapsed OCD-patients.

The inclusion procedure implies that all relevant patients in Norway in the given time period will be offered participation. If this population turns out to be fewer than 160 patients during the study period, the inclusion period might be extended six months. If less than 160 patients are included at that point, analyses will be performed on the number of patients included by the end of the study period.

### 5.1 Inclusion Criteria

- Outpatients
- $\geq 18$  years
- Fulfilling diagnostic criteria of OCD according to the DSM-5
- Previously have received ERP-treatment delivered by trained therapist and either have responded and relapsed, or not responded to the treatment.
  - Response is defined by  $\geq 35\%$  reduction with a post-treatment Y-BOCS score of 15, followed by a relapse as defined by  $> 35\%$  increase in Y-BOCS score from post-treatment, a Y-BOCS score of 16 or more, and a CGI-I score of 6 ("much worse") or higher.
  - Non-responders are defined as those with a reduction in Y-BOCS scores from pre- to post-of less than 35%, and with a minimum Y-BOCS score of  $\geq 16$  after treatment. In order to be classified as non-responder as opposed to "drop-out" the patient has to previously have received a minimum of 6 sessions.
- There must be a minimum of 4 weeks since treatment ended.
- Fluent in Norwegian
- Signed informed consent

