## Protocol Summary

| PROTOCOL IDENTITY AND OBJECTIVES       |                                                                                                                                                                                                                                                                                 |
|-----------------------------------------------|---------------------------------------------------------------------------------------------------------------------------------------------------------------------------------------------------------------------------------------------------------------------------------|
| EudraCT Number:                               | 2013-002574-49                                                                                                                                                                                                                                                                  |
| Protocol Title:                               | Translational approach to the understanding and treatment of Obsessive-Compulsive Disorder (OCD). Can D-Cycloserine enhance and stabilize the treatment-response in relapsed and non-responding OCD-patients?
A randomized, double-blind, placebo- controlled national study |
| Trial Objective:                              | Investigate whether DCS gives incremental effects to concentrated exposure in vivo with response prevention (ERP) in terms of reduced OCD symptoms and reduced relapse rate on follow-up in previously relapsed or non-responding OCD patients.                                 |
|                                               |                                                                                                                                                                                                                                                                                 |
| INVESTIGATIONAL MEDICINAL PRODUCTS (1) |                                                                                                                                                                                                                                                                                 |

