| Primary Endpoint:                             | Changes in OCD symptoms from pre-treatment (T0) to post-treatment (T1) as well as 3-months (T2), 12 months (T3) and 5-year follow-up (T4).                                                                                                                                      |
| Efficacy Parameters:                          | Remission in diagnostic status according to the Structured Clinical Interview for DSM-5 Axis I disorders (SCID-I) criteria for OCD and Clinician administered Y-BOCS interview by specially trained and blinded assessors.                                                      |
| Safety Parameters:                            | Adverse Events (AE) and Serious Adverse Events (SAE) assessed during the active treatment days, at post-treatment, 3-months (at clinic), 12 months and 5 years follow-up using telephone clinician assessments.                                                                 |
|                                               |                                                                                                                                                                                                                                                                                 |
| POPULATION OF TRIAL SUBJECTS           |                                                                                                                                                                                                                                                                                 |
| Description of Trial Subjects:                | Patients with a primary diagnosis of OCD according to the DSM-5 who have partially or fully relapsed, or not responded from standard ERP-treatment delivered by trained therapists.                                                                                             |
| Number of Subjects:                           | 160 patients with OCD                                                                                                                                                                                                                                                           |

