### 13.2 Determination of Sample Size

A meta-analysis by Norberg, Krystal & Tolin [69] found a medium effect size for ERP + DCS for heterogeneous samples of OCD-patients. However, in the current study, only patients who have relapsed after an initially successful ERP-treatment will be included. This is a sample which supposedly increases the possibility to detect DCS-effects and we assume that the effect size would be larger than that found in previous studies. In order to have 80% power to detect a moderate effect size ( $d = 0.50$ ) at an alpha-level of 0.05 a total of 160 patients will be included (64 in each of the DCS-conditions and 32 in the Placebo group). Patients lost or withdrawing from the study will be treated as drop-outs and replaced. We estimate an increased sample size of 10 patients, in total, to compensate for possible drop-outs.

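### Section 5.1 sets prior response at a Y-BOCS score of exactly 15, which clashes with its own relapse rule, and section 13.2 describes a relapsers-only sample that the trial does not enrol

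*Protocol*

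**What the plan says.** Section 5.1 admits patients who have had ERP and "either have responded and relapsed, or not responded to the treatment". Two routes follow.

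- **Relapser.** The earlier course must have produced a ≥35% "reduction with a post-treatment Y-BOCS score of 15, followed by a relapse as defined by" a rise of more than 35%. The relapse part reads in full as a >35% "increase in Y-BOCS score from post-treatment, a Y-BOCS score of 16 or more, and a CGI-I score of 6" or higher.
- **Non-responder.** The earlier course gave "a reduction in Y-BOCS scores from pre- to post-of less than 35%, and with a minimum Y-BOCS score of" 16 or more, after at least 6 sessions.

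The Protocol Summary describes the same two groups. Its objective refers to "previously relapsed or non-responding OCD patients", and its description of subjects covers patients "who have partially or fully relapsed, or not responded from standard ERP-treatment delivered by trained therapists". The objective at the end of section 3 and the opening of section 5 also name both groups.

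Section 13.2 differs. It says that "only patients who have relapsed after an initially successful ERP-treatment will be included". From this it argues that a DCS effect should be easier to detect and that the effect should exceed that of earlier studies. It then powers the trial for d = 0.50 with 160 patients.

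**The concern.** The cut-offs in 5.1 are working rules. Under section 8.2 a national team checks each consenting patient's prior Y-BOCS scores against them, and section 7.1 provides a checklist form that summarises all the criteria. A threshold written as a single value is either applied as written, which shuts out the better earlier responders who later relapsed, or silently reinterpreted, which may differ between assessors. Section 5 already foresees that fewer than 160 patients may be found nationally, so entry lost to a wording slip would matter.

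The second issue concerns what the sample-size section can claim. If non-responders are enrolled, an expectation argued from a relapsers-only sample does not describe this trial's population.

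**Working it through.** The protocol gives no figure to reproduce here. The check sets its rules against one another, using whole-number Y-BOCS totals from 0 to 40 (section 7.1).

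**1. Does a response score of exactly 15 fit the relapse rule?**

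Relapse needs a rise of more than 35% from the post-treatment score and also a score of 16 or more. The lowest score meeting the percentage condition is the first whole number above 1.35 × the post-treatment score:

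| Earlier post-treatment score | 1.35 × score | Lowest score with >35% rise | Does the 16-or-more condition add anything? |
|---|---|---|---|
| 10 | 13.5 | 14 | yes |
| 11 | 14.85 | 15 | yes |
| 12 | 16.2 | 17 | no |
| 14 | 18.9 | 19 | no |
| 15 | 20.25 | 21 | no |

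The 16-or-more condition has work to do only when the earlier course ended at 11 or less. The literal response rule excludes all of those scores. Under it the condition is dead text; under 15 or lower it does its job. Since non-response requires 16 or more, 15 or lower is also the natural counterpart on the response side.

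**2. How narrow is the literal rule?**

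Among scores 0 to 15 it accepts one value and rejects fifteen (0 to 14). Reaching exactly 15 with a ≥35% reduction needs a baseline of at least 15 / 0.65 = 23.1, that is, 24 or more. These are counts of possible scores, not shares of patients.

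**3. Which population does each section describe?**

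| Place | Relapsers | Non-responders |
|---|---|---|
| Protocol Summary, objective | yes | yes |
| Protocol Summary, subjects | yes | yes |
| Section 3, objective | yes | yes |
| Section 5, opening | yes | yes |
| Section 5.1 | yes | yes |
| Section 13.2 | yes | no |

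Section 13.2 stands alone.

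**4. What does the contradiction do to the sample size?**

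Section 13.2 first cites a medium effect from a meta-analysis of heterogeneous OCD samples. It then adds that the relapser sample should do better, and finally powers for a moderate d = 0.50. The relapser sentence supports an expectation above the planning value, not the planning value itself. Removing it leaves 0.50 and 160 as they are.

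**5. Which score pairs fall under neither route, once 15 is read as 15 or lower?**

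- *Reduction of ≥35% with a score of 16 or more.* This needs 0.65 × baseline ≥ 16, so baseline ≥ 24.6, that is, 25 or more. At baseline 25 the only such score is 16 (0.65 × 25 = 16.25). At 30 they are 16 to 19 (19.5), and at 40 they are 16 to 26 (26.0).
- *Reduction below 35% with a score of 15 or less.* For example 23 to 15: 8 / 23 = 34.8%.

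**The case against.** The best defence is that the intended meaning is obvious. The inconsistency shown above itself points to 15 or lower, assessors would probably read it that way, and section 8.2 sends questionable cases to two senior investigators for consensus. A sign lost when the PDF was read also cannot be wholly excluded. Part of this stands: the harm depends on the literal text being followed. But the other inequality signs in the same bullet and the next survive, and a consensus step names who decides without supplying the rule. An entry threshold should not need reinterpreting.

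Four stronger readings are tempting, and the protocol does not support them.

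- A reader might infer that most relapsers are excluded. No distribution of earlier scores is given, so the share is unknown.
- A reader might infer that d = 0.50, and so the sample size, rests on a relapsers-only sample. It follows the cited medium effect in heterogeneous samples. The idea that DCS helps most where psychological treatment worked less well, set out in section 3, could also extend to non-responders.
- A reader might infer that leaving out patients with a ≥35% reduction and a score of 16 or more is an error. They meet neither route and so are determinately ineligible. Eligibility groups need not cover every score, and this may be a design choice.
- A reader might infer that results by relapser or non-responder type must be specified here. That can be left to the SAP, which is not at hand, and with 32 placebo patients such results would be imprecise.

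**Conclusion.** Two defects hold. The response threshold in 5.1 is wrong as written: taken literally it bars every relapser whose earlier course ended at 0 to 14, and it makes another condition of the same rule redundant. Section 13.2 misdescribes the population, against five other statements in the protocol, and so loses its stated reason for expecting a larger effect than in earlier studies.

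The first conclusion rests on the printed text having no inequality sign and on whole-number scoring; its effect on accrual cannot be quantified. The second changes no planned number. The score pairs that fit neither route call for clarification only.

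**What to change.** - **Section 5.1 and the inclusion checklist:** state the prior-response score as 15 or lower, to match the protocol's own 16 or more for relapse and non-response.
- **Section 13.2:** describe the sample as relapsed or non-responding. Drop the statement that a relapsers-only sample should give a larger effect, or argue it afresh for the population enrolled. Leave 160 and d = 0.50 unchanged.
- **Clarification only:** confirm in a sentence whether patients with a ≥35% reduction but a score of 16 or more, and those with a smaller reduction but a score of 15 or less, are meant to be ineligible.

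The cost is a wording amendment to the protocol and the form. No new data are needed, because section 9.4 already collects the prior Y-BOCS scores. If the clarification led to admitting either group, the eligible population would change and ethics approval under section 15.1 might be needed. Confirming that they are ineligible costs one sentence.
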